| WHODAS2.0 | World Health Organization Disability Assessment |
| SRQ-20 | Self-Report Questionnaire |
| ACOK | Screen for Co-Occuring Disorders |
| PSYCHLOPS | Psychological Outcome Profiles |

1. **Synopsis**

| **Sponsor/Sponsor-Investigator** | [name] |
| --- | --- |
| **Co-Principal Investigator** | [name] |
| **Study Title** | The impact of PM+FM intervention on improving mother’s mental health in Zambia |
| **Short Title/Study ID** | PM+FM |
| **Protocol Version and Date** | Version 1.1; 29.10.2022 |
| **Trial Registration** | Pending – will be registered on Clinicaltrials.gov |
| **Study Category with** **Rationale** | Other Clinical Trials, Category A  Rationale:  - Research project in which persons are prospectively assigned to a health-related intervention in order to investigate its effects on health or on the structure and function of the human body.  - Definition of Health (WHO): Health is a state of complete physical, mental and social well-being and not merely the absence of disease or infirmity |
| **Clinical Phase** | Not applicable. Not a clinical trial with drugs. |
| **Background and Rationale** | CMHD are particularly prevalent among women, posing a major threat to their own and their children’s wellbeing. In Zambia, our research team found that around 28% of women suffer from anxiety or depression.  Despite the high prevalence of CMHD and the existence of effective treatments, interventions supporting women living in low-resourced settings remain limited. Recent community-based programs have succeeded in cost-effectively tackling minor mental health problems, but have not helped individuals with severe symptoms.  This study builds on a parent study (Zamcharts), which identified a high prevalence of women with anxiety and/or depression. We propose to design, test and validate a community-based intervention nested within the public primary health system in Zambia, as a mental health care delivery platform to identify and treat women with mild-to-severe CMHDs. We aim to demonstrate the impact of integrating high-quality mental health care in the national system. |
| **Objective(s)** | To 1) adapt the Problem Management plus program to sub-Saharan mothers living in Zambia and to 2) assess the acceptability, feasibility and potential efficacy of the resulting intervention in reducing mental health symptoms and promoting positive maternal-child relationship among women taking care of young children in Lusaka, Zambia. |
| **Outcome (s)** | The primary study outcomes will be 1) number of sessions of PM+ attended (acceptance of the program = >50% of sessions attended; feasability within the local context = ≥ 1 session attended and offered and participants’ and providers’ qualitative feedback) and 2) improve their mental health status (overall mental health symptoms by SRQ-20 <7; Hopkins Symtpoms checklist reduction (% of cutoff <1.0.6),  Secondary outcomes: Patient Health Questionnaire (PHQ-9) (0-27; cutoff score, >10) for depressive symptoms; Generalized Anxiety Disorder Scale (GAD-7) score range, 0-21; cutoff score, >10) for generalized anxiety symptoms; Psychlops, psychological outcome profiles (designed to evaluate problem management plus intervention) and World bank toolkit on child-mother relationship. |
| **Study Design** | Randomised control trial |
| **Inclusion/Exclusion Criteria** | All mothers enrolled in Zamcharts clinical trial (n=790) with SRQ-20>7.  Exclusion criteria:   - Mothers who plan to migrate out of the study area within 6 months of the enrolment date - Mothers with severe substance use symptoms, bipolar disorder or squizophrenia - Mothers receiving psychotherapy elsewhere |
| **Measurements and Procedures** | From the total of 265 mothers residing in Lusaka district participating in the ZamCharts study and with mental health needs, we will divide them into two groups:  a control group a intervention group  All women will be called for a screening interview and then, if eligible, invited to receive a baseline interview followed by the intervention (provided in health facilities, by phone and at home) at the beginning and an endline interview at the end of the study.  Families in the intervention group will receive a locally adapted version of the Problem-Management Puls intervention developed by WHO after the baseline interview that allows them to better manage life stressors. The intervention will be provided by trained community health workers, started in groups (1^st^ session) and then continued individually by phone, or in-person at health facilities or at women’s home.  Severe cases will be referred to psychiatry services to evaluate need of antidepressants. |
| **Study Product/Intervention according to KlinV, if applicable** | This study will test an intervention: Problem Management+For Moms (PM+FM) program to reduce mental health symptoms among women and increase mother-child interaction |
| **Comparator(s) (if applicable)** | The comparator for the interventions is standard local caregiving (no intervention) among mothers participating in the Zamcharts clinical trial |
| **Study Duration** | 9 Months |
| **Participants** | A total of 265 caregivers and their children are expected to participate in the study. |
| **Study Schedule** | Sept. 2022: study setup, software development and IRB approval. Identification of WCW  Sept. 2022 – Nov. 2022: Training of 3-5 WCW  Nov. 2022: Enrollment of participants. Screening.  Dec. 2022 – April 2023: implementation of interventions  April 2023: Endline assessments  May 2023 - December 2023: Data analysis & dissemination |
| **Study Centre(s)** | The study will be coordinated by the PIs, and implemented by Innovations for Poverty Action Zambia in direct collaboration with the Zambian Ministry of Health and the department of psychiatry of the University Teaching Hospital in Lusaka. |
| **Statistical Considerations & Power calculations** | The study is statistically powered to detect a 0.25 SD improvement in SRQ-20 over an 6-month period between mothers receiving the PM+FM and mothers not receiving the intervention, assuming α=0.05, a follow-up rate of 85% (attrition < 15%), and an intra-class correlation coefficient (ICC) of 0.05 . The estimated improvement is based on the results from similar studies. |
| **Ethical Statement** | This study will be conducted in compliance with the protocol, the current version of the Declaration of Helsinki, KFPE principles for transboundary research as well as all national legal and regulatory requirements. |

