# Study design

We propose to conduct a trial with mothers in Lusaka district. This area was selected to ensure feasibility of the study. Lusaka is an urban area with relatively easy access to care and transportation.

This is a pilot study nested within the “THE IMPACT OF GROWTHCHARTS ON STUNTING AND CAREGIVER AWARENESS: RESEARCH AND POLICY ENGAGEMENT FOR POTENTIAL SCALING (REF. NO. 1411-2020)” clinical trial using a mix-methods analysis. 790 caregiver-child dyads were enrolled in this study in Lusaka in 2021; 30% of these women displayed mild to severe symptoms of depression and/or anxiety (SRQ-20 ≥ 8). For this feasibility study, we will randomly select women from this subgroup. All selected women will be contacted and reassessed with the Self-Reporting Questionnaire (SRQ-20) and further assessed using the Hopkins Symptoms Checklist-25 items^11-13^.

Final ***eligibility*** will be determined by 1) SRQ-20 >7 (clinically significant symptoms of depression or/anxiety anxiety), 2) women with 1 hour a week availability not planning to move within the next 6 months, 3) capacity to consent and 4) not receiving current mental health care. Individuals with active suicidal ideation (determined by Paykel scale^14^), severe substance use (ACOK-SUD >4),^15^ mania or psychotic symptoms^16^ will be excluded and referred to primary care provider or partnering psychiatrist (for emergency cases). We expect that around 70 caregivers will meet the inclusion criteria for the mental health feasibility study. All selected women from the intervention group will be contacted and reassessed with the Self-Reporting Questionnaire (SRQ-20) and the Hopkins Symptoms Checklist 25.

Eligible individuals will continue with a Baseline interview to assess main outcome measures. We plan to focus on engaging participants in each of the research components of the trial (assessments and sessions) through systematic engagement protocol including regular calls to participants and home visits after two weeks of non-responsiveness. All eligible subjects will be randomized with probability of 0.5 to either treatment or control group. Randomization will be based on a random draw generated by the senior author (GF) using the Stata SE 16.0 statistical software package.

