## 7.2. Sample size calculation

This is a pilot study nested within the “The impact of growthcharts on stunting and caregiver awareness: research and policy engagement for potential scaling (ref. no. 1411-2020)” clinical trial. 800 caregiver-child dyads were enrolled in this study in Lusaka in 2021; 28% of these women displayed mild to severe symptoms of depression and/or anxiety (SRQ-20 ≥ 8). For this feasibility study, 30% of the women enrolled in the parent trial displayed mild to severe symptoms of depression and/or anxiety (SRQ-20 ≥8). For this study, we expect an attrition rate of 13% based on previous studies. With an expected analytical sample size of 100 women per arm we are powered to detect an intent-to-treat difference of 20 percentage points in the prevalence of depression at endline with power 0.8, and 23 percentage point difference in depression with power 0.9. We are aware that for the current trial we are not powered to detect small effect size. Thus, we will only explore the efficacy of the intervention to generate some preliminary efficacy estimates that will serve us to power and elucidate the needed sample size for a larger effectiveness trial.

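### The synopsis claims power for 0.25 SD that no stated sample size delivers, and the forecast of about 70 eligible women cannot be reconciled with 200 analysed or 265 participating

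*Protocol*

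**What the plan says.** The Synopsis, under statistical considerations, says: "The study is statistically powered to detect a 0.25 SD improvement in SRQ-20 over an 6-month period". It assumes alpha 0.05, 85% follow-up and an "intra-class correlation coefficient (ICC) of 0.05". It gives no power level, sidedness, cluster unit or cluster size. Under Participants it says: "A total of 265 caregivers and their children are expected to participate in the study". Under Measurements and Procedures the same number appears as a pool that is split into two groups ("From the total of 265 mothers residing in Lusaka district participating in the ZamCharts study and with mental health needs"), with screening for eligibility described afterwards.

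Section 7.2 uses a different effect and a different number: "With an expected analytical sample size of 100 women per arm we are powered to detect an intent-to-treat difference of 20 percentage points" at power 0.8, or 23 points at power 0.9, with 13% attrition. It then concedes that "we are not powered to detect small effect size" and that efficacy will only be explored.

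Study design and Exclusion criteria both say: "We expect that around 70 caregivers will meet the inclusion criteria for the mental health feasibility study". Both also say that all eligible women are randomised with probability 0.5.

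The parent-trial pool is given as 790 women with 30% screening positive (Study design) and as 800 with 28%, then 30% (section 7.2). Attrition is 13% in section 7.2 and 15% in the Synopsis and under Discontinuation of individual participants.

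**The concern.** Two things conflict. First, 0.25 SD is a small standardised effect. The synopsis presents it as detectable, while section 7.2 says that small effects are not. Second, the expected number of women differs too much between sections for attrition to explain it: about 70 eligible cannot become 200 analysed.

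The synopsis is the part most readers rely on, and its power statement carries no caveat. Someone who takes it at face value could read a null SRQ-20 result as evidence against an effect of 0.25 SD when the trial had roughly an even chance, or much less, of detecting one. A reader also cannot tell what precision to expect, which matters because the efficacy estimates are meant to size a larger trial.

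**Working it through.** **Inputs from the protocol.** Effect 0.25 SD, alpha 0.05, follow-up 85%, ICC 0.05, 265 participants (Synopsis); 100 analysed per arm, 20 points at 0.8, 23 points at 0.9, attrition 13% (section 7.2); about 70 eligible, randomised 1:1 (Study design, Exclusion criteria).

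**Assumed, because not stated.** Two-sided test, control-arm rate, cluster size, correlation with baseline.

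**1. Section 7.2's own figures.** For two proportions with n per arm, power = Φ{[d − 1.96·√(2p̄(1−p̄)/n)] / √[(p₁q₁ + p₂q₂)/n]}. The least favourable control rate is about 0.60.
- 20 points, 0.60 vs 0.40, n = 100: Φ(0.886) = 81%.
- 23 points, 0.60 vs 0.37, n = 100: Φ(1.330) = 91%.

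Both claims reproduce.

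**2. The 0.25 SD claim.** Power = Φ(0.25/√(2/n) − 1.96).

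| Analysed | n per arm | 0.25/√(2/n) | Power | Detectable at 80%: 2.80·√(2/n) |
|---|---|---|---|---|
| 265 (no attrition) | 132.5 | 2.03 | 53% | 0.34 SD |
| 265 × 0.85 = 225 | 112.6 | 1.88 | 47% | 0.37 SD |
| 200 | 100 | 1.77 | 42% | 0.40 SD |
| 70 (no attrition) | 35 | 1.05 | 18% | 0.67 SD |
| 70 × 0.87 = 61 | 30.5 | 0.98 | 16% | 0.72 SD |

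Required for 80%: n = 2 × (1.96 + 0.84)²/0.25², about 252 per arm or 504 analysed. At 15% attrition that is 504/0.85 = 593 enrolled.

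Sensitivity at 225 analysed:
- One-sided test: 59%.
- ICC 0.05 with design effect 1 + (m − 1) × 0.05 in both arms: 45% for m = 2, 40% for m = 5, 27% for m = 20.
- Baseline adjustment, replacing the SD by SD·√(1 − r²): about 81% only if r is about 0.75 and there is no clustering.

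**3. The numbers of women.**
- Randomised needed for 200 analysed: 200/0.87 = 230, or 200/0.85 = 235.
- Analysed from 70 randomised: 70 × 0.87 = 61, or 70 × 0.85 = 60, so about 30 per arm.
- Screen-positive pool: 790 × 0.28 = 221 up to 800 × 0.30 = 240. The figure 265 exceeds this; 265/790 = 33.5%, a prevalence stated nowhere.

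**4. Section 7.2's effects if about 70 is right.** At about 30 analysed per arm and control rates of 50-80%:
- Power is about 34-40% for 20 points and 43-49% for 23 points.
- The detectable difference at 80% power is about 33-36 points.

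**5. Precision.** The 95% half-width is 1.96·√[(p₁q₁ + p₂q₂)/n]. For 0.60 vs 0.40 it is about 14 points at 100 per arm and about 25 points at 30 per arm.

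**The case against.** Much can be said for the protocol.

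- **The percentage-point claims.** A reader might infer that neither power claim holds. That goes too far. The 20- and 23-point claims are right at their stated 100 per arm. With 265 randomised and 85% followed up, power for 20 points would be at least 86%. They fail only if about 70 is the true number, and the protocol does not settle that.
- **265 and 200.** A reader might see three mutually incompatible sizes. But these two can be stages of one flow: a 13% loss at screening and then 13% attrition gives 265 × 0.87 × 0.87 = 201. The synopsis uses 265 both as a pool and as expected participants, which is loose. The hard conflict is with 70.
- **Origin of the 100 per arm.** It lies close to all parent-trial positives less attrition (800 × 0.28 × 0.87/2 = 97; 790 × 0.30 × 0.85/2 = 101). One might conclude that no screening loss was allowed for, but section 7.2 gives no derivation, so this stays a guess.
- **Clustering.** It is tempting to tie the ICC to the community workers who deliver the sessions. The protocol names no cluster unit, and enumeration areas are equally possible. Only a range over assumed cluster sizes is defensible.
- **The exploratory caveat.** Section 7.2 calls efficacy exploratory, and the feasibility and acceptability measures do not depend on this calculation. That lowers the stakes. It does not remove the contradiction, because the synopsis carries no such caveat.

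Could the 70 be the intervention arm alone? The text says all eligible women are randomised to either group, and even then 70 × 0.87 = 61 falls short of 100.

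**Conclusion.** The concern holds in two parts. The 0.25 SD claim is unsupported at every stated sample size: power is 53% at best and 47% under the synopsis's own follow-up. It omits the power level and contradicts section 7.2. This rests on a two-sided test and no baseline adjustment. A one-sided test does not rescue it, and only an undocumented baseline correlation of about 0.75 without clustering would.

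The forecast of about 70 eligible women cannot be reconciled with 200 analysed or 265 participating, and 265 exceeds the 221-240 women that the protocol's prevalence figures imply. The documents do not show which number is right, so the loss of power for 20 and 23 points is conditional on 70 and on control rates of 50-80%. It should be fixed; the exploratory status of efficacy keeps it from being more serious.

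**What to change.** - Delete the 0.25 SD sentence from the Synopsis, or replace it with the effect detectable at 80% power for the reconciled number: about 0.37 SD at 225 analysed, 0.40 SD at 200, or about 0.7 SD at 60-70.
- Give one expected flow, used everywhere: positive in the parent trial, re-screened, eligible, randomised, analysed. Use one parent-trial total, one prevalence and one attrition figure.
- Restate section 7.2 for the resulting number. Name the power level, sidedness and assumed control rate. Give the expected confidence-interval width. Either state the cluster unit and size behind the ICC or drop the ICC.
- Repeat the exploratory caveat in the Synopsis.

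The cost is protocol wording only. No extra women are needed. The stated power becomes less favourable.

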# Background information

## Introduction

Mental health disorders affect millions of mothers in low-and-middle income countries (LMICs), limiting their ability to care for themselves and their children. Effective treatments for mental health disorders are widely available in high-income countries, but rarely applied in LMIC settings. Through this pilot, we aim to show that high-quality mental health support is possible in low-resource settings by combining community-based programming with targeted triaging to higher-level care. If successful, this evidence can provide a first step to improved mental health care in Zambia and many other settings.

Psychosocial programs integrated in PC systems increase access while providing treatment of minor CMHD within the community. However, in LIMC, the lack of supporting health policies and long-term resources limit their long-term effect. Moreover, they are not sufficient to treat severe cases. For those, pharmacological treatment is the most effective and considered the first treatment option but, in Zambia, systems are not in place to properly identify them and there is no data on the delivery of psychiatric medication within PC.

We propose to develop and pilot a mental health program and delivery platform for a set of interventions in Zambia to reduce the impact of CMHD disorders among women with young children, building upon the existing PC system and available evidence-based practices.

## Objectives and purpose

The long-term goal of this pilot study is to implement, if found effective, the EM-PM+ intervention within the primary care health system at the national level.

Primary objective**.** We aim to design, test and implement an evidence-based pilot mental health care program integrated within the primary health system for reducing mental health burden among mothers in Lusaka

Secondary objectives**.**

a. To evaluate the acceptability, feasibility and potential efficacy of a culturally sensible evidence-based intervention, the Expanded for Moms-Problem Management Plus (EM-PM+) in reducing mental health symptoms and promoting positive maternal-child relationship among women taking care of young children in Lusaka, Zambia compared to the best locally available care in reducing mental health burden among mothers in Lusaka and improving child development.

c. To build local capacity on mental health access in Lusaka for long-term impact.

e. To produce and disseminate high-quality international scientific publications with the highest ethical standards on the project findings to improve the evidence of mental health interventions in LMICs.

We hypothesize that 1) the EM-PM+ will be accepted by offered individuals (measured as >50% of sessions attended, satisfaction measure and qualitative feedback), 2) the EM-PM+ is feasible within the local context (measured by ≥ 1 session attended and offered and participants’ and providers’ qualitative feedback), 3) individuals receiving the EM-PM+ intervention will improve their wellbeing through improvement of mental health status and maternal-child relationship.

## Scientific justification and rationale of study population

As stated above, mental health disorders are highly prevalent worldwide and a leading cause of disability^1^. Depression and anxiety are the most common disorders with over 300 million cases worldwide. ^2,3^ Mental health disorders result from a complex interaction of social, psychological and biological factors and their development is related to chronic stress exposure as well as to acute trauma experiences. In Zambia, recent data from the our team suggest high rates of distress among women in charge of young children, however, common mental health disorders remain unnoticed and mainly untreated.^4^ The public healthcare system in Zambia, similar to other neighboring LMICs, offers only very limited mental health services. Existing mental health care and mental health workforce mainly focus on attending people with severe mental illness such as schizophrenia, other forms of psychosis and severe behavioral disorders. This care is concentrated in a few psychiatric institutions which are permanently full^5^. Undetected and untreated mental health problems n adversely affect women and their children in many ways, including reduced wellbeing and quality of life, increased food insecurity and reduced engagement with children, which can result in slower child development and an increased risk of anxiety, reduced physical growth, cognitive impairment^6^ and higher risks of non-adherence to HIV treatment for both.^7^ Zambia, faces several challenges in addressing such common mental health disorders within the primary care system. Shortage of mental health professionals, unmet training needs and lack of evidence-based psychosocial interventions adapted to the local context are currently the most important obstacles to serve this population. Evidence suggests that culturally adapted psychosocial programs, delivered by trained paraprofessionals or community health workers (CHWs), can be effectively integrated in healthcare systems, increasing mental health access and workforce capacity ^8,9^ while allowing the provision of evidence-based practice to treat common mental health disorders within the primary care setting along with other non-communicable diseases.^10^

In Zambia, preliminary data collected by our research team suggest that 28% of mothers are in mental distress, one quarter of whom have severe symptoms. Like in many other LMICs, mental health resources are limited and mainly concentrated in a few psychiatric institutions focused on caring for severe illnesses such as schizophrenia. Most CMHDs remain undiagnosed and untreated as primary care (PC) systems are not equipped to address mental health needs of the population.

Evidence suggests that culturally adapted psychosocial programs, delivered by community health workers (CHWs), can be integrated in healthcare systems, increasing mental health access and workforce capacitywhile allowing the provision of evidence-based practice to treat mild to moderate common mental health disorders within the primary care setting along with other non-communicable diseases. However, two important obstacles hinder the implementation of psychosocial interventions within most sub-Saharan regions, including Zambia: 1) the lack of available culturally adapted evidence-based interventions tackling women with small children, 2) the treatment of those with severe symptoms.

First, even though the proven effectiveness of some psychosocial interventions in treating mild to moderate mental health symptoms, there are no tested treatments adapted to women in charge of young children living in low income settings. Second, around 30% of people with CMHD suffer severe symptoms which heavily impair the capacity to develop daily tasks including low performance in parenting activities, domestic duties and self-care routines including their capacity to engage in psychosocial intervention sessions. For those cases, regardless of the economic development of the country, pharmacological treatment is the first treatment option. However, even though there are generic medications, at a low cost and available in all areas of the world there is very little data on the effectiveness, training in use and management of psychotropic medication within the primary health system of low-income settings.

Our proposed project, lead by a clinical psychiatrist collaborating with a local team of clinicians and policy makers, will overcome these challenges by 1) testing a multi-level intervention that adequately identifies and treats women with mental health symptoms, no matter their severity

The feasibility, acceptability and effectiveness of this multi-level intervention will be pilot tested through a clinical trial design.

